## 5.0 Initial Screening Questions - Updated 9/13

(Note: You must answer every question on this page to proceed).

If you are converting to the new form, check questions 5.4, 5.6, 5.7, 5.8 and 5.10 before saving and continuing to the next section.

### 5.1 \* Application type:

- ☐ Full Committee  
☒ Expedited  
☐ Exempt

### 5.2 \* Risk level (Help Text updated 9/13):

- ☒ Minimal risk  
☐ Greater than minimal risk

### 5.3 \* Subject contact:

- ☒ Yes (including phone, email or web contact)  
☐ No (limited to medical records review, biological specimen analysis, and/or data analysis)

### 5.4 \* Funding (past or present):

- ☒ Funded or will be funded (external sponsor, gift, program or specific internal or departmental funds)  
☐ Unfunded (no specific funds earmarked for this project)  
☐ Unfunded student project

### 5.5 \* The Principal Investigator and/or one or more of the key study personnel has financial interests related to this study:

- ☐ Yes ☒ No

If **Yes**, the Conflict of Interest Advisory Committee (COIAC) office may contact you for additional information.

### 5.6 \* This is an investigator-initiated study:

- ☒ Yes ☐ No

### 5.7 \* This study ONLY involves retrospective records review and/or identifiable biospecimen analysis:

- ☐ Yes ☒ No

### 5.8 \* This is a clinical trial:

☒ Yes ☐ No

### Clinical Trial Registration

"NCT" number for this trial:

NCT02746393

#### 5.9 \* This is a multicenter study:

☐ Yes ☒ No

#### 5.10 \* This application involves the study of unapproved or approved drugs, devices, biologics or in vitro diagnostics:

☐ Yes ☒ No

#### 5.11 \* This application involves a Humanitarian Use Device:

- ☒ No  
☐ Yes, and it includes a research component  
☐ Yes, and it involves clinical care ONLY

#### 5.12 \* This study involves human stem cells (including iPS cells and adult stem cells), gametes or embryos:

- ☒ No  
☐ Yes, and requires CHR and GESCR review  
☐ Yes, and requires GESCR review, but NOT CHR review

#### 5.13 \* This is a CIRB study (e.g. the NCI CIRB will be the IRB of record):

☐ Yes ☒ No

#### 5.14 \* This application includes a request to rely on another IRB (other than NCI CIRB):

☐ Yes ☒ No

Note: If this request is approved, the CHR will **NOT** review and approve this study. Another institution will be the IRB of record.

## 6.0 Expedited Review Categories

#### 6.1 \* If you think this study qualifies for expedited review, select the regulatory category(ies) that the research falls under:

- ☐ Category 1: A very limited number of studies of approved drugs and devices  
☐ Category 2: Blood sampling  
☒ Category 3: Noninvasive specimen collection (e.g. buccal swabs, urine, hair and nail clippings, etc.)  
☐ Category 4: Noninvasive clinical procedures (e.g. physical sensors such as pulse oximeters, MRI, EKG, EEG, ultrasound, moderate exercise testing, etc.)  
☐ Category 5: Research involving materials (data, documents, records, or specimens) that were previously collected for either nonresearch or research purposes  
☐ Category 6: Use of recordings (voice, video, digital or image)

- ☒ Category 7: Low risk behavioral research or research employing survey, interview, oral history, focus group, program evaluation, human factors evaluation, or quality assurance methodologies

## 7.0 Funding

**7.1 Identify all sponsors and provide the funding details. If funding comes from a Subcontract, please list only the Prime Sponsor:** **Note: we require only a P Number OR an A Number for funding coming through UCSF. Please avoid these common errors in funding documentation:**

- DO NOT add the A Number if a P Number was already provided OR update the A Number field when a new funding cycle begins. The IRB does NOT use this information or want these changes made.**
- DO NOT add a grant continuation as a new funding source.**

External Sponsor:

| View Details             | Sponsor Name        | Sponsor Type | Awardee Institution | Contract Type: | UCSF RAS "P number" or eProposal number | UCSF RAS System Award Number ("A" + 6 digits) |
|--------------------------|---------------------|--------------|---------------------|----------------|-----------------------------------------|-----------------------------------------------|
|  | JPB Foundation, The | 07           | UCSF                | Subcontract    | P0527438                                |                                               |

|                                                                 |                                             |
|-----------------------------------------------------------------|---------------------------------------------|
| Sponsor Name:                                                   | JPB Foundation, The                         |
| Sponsor Type:                                                   | 07                                          |
| Sponsor Role:                                                   | Funding                                     |
| Grant/Contract Number:                                   |                                             |
| Awardee Institution:                                            | UCSF                                        |
| Is Institution the Primary Grant Holder:                 | No                                          |
| if No, then who is the Primary Grantee?                  |                                             |
| Contract Type:                                                  | Subcontract                                 |
| UCSF RAS "P number" or eProposal number:                        | P0527438                                    |
| UCSF RAS System Award Number ("A" + 6 digits):                  |                                             |
| Grant Number for Studies Not Funded thru UCSF:                  |                                             |
| Grant Title:                                                    | Research Network on Toxic Stress and Health |
| PI Name:
(If PI is not the same as identified on the study.) | [name] [name]                    |
| Significant Discrepancy:                                        |                                             |

|                                                                                     |                     |                     |      |             |          |  |
|-------------------------------------------------------------------------------------|---------------------|---------------------|------|-------------|----------|--|
| [figure not shown] | JPB Foundation, The | 07                  | UCSF | Subcontract | P0537151 |  |
| Sponsor Name:                                                                       |                     | JPB Foundation, The |      |             |          |  |
| Sponsor Type:                                                                       |                     | 07                  |      |             |          |  |
| Sponsor Role:                                                                       |                     | Funding             |      |             |          |  |

|                                                                 |                                             |
|-----------------------------------------------------------------|---------------------------------------------|
| Grant/Contract Number:                                   |                                             |
| Awardee Institution:                                            | UCSF                                        |
| Is Institution the Primary Grant Holder:                 | Yes                                         |
| Contract Type:                                                  | Subcontract                                 |
| UCSF RAS "P number" or eProposal number:                        | P0537151                                    |
| UCSF RAS System Award Number ("A" + 6 digits):                  |                                             |
| Grant Number for Studies Not Funded thru UCSF:                  |                                             |
| Grant Title:                                                    | Research Network on Toxic Stress and Health |
| PI Name:
(If PI is not the same as identified on the study.) | [name]                                  |
| Significant Discrepancy:                                        |                                             |

Gift, Program, or Internal Funding (check all that apply):

- ☒ Funded by gift (specify source below)
- ☒ Funded by UCSF or UC-wide program (specify source below)
- ☐ Specific departmental funding (specify source below, if applicable)

List the gift, program, or departmental funding source:

Pritzker Family Fund; Harvard Research Network; RAPtr; UCB Joint Medical Program

## 7.2 If you tried to add a sponsor in the question above and it was not in the list, follow these steps:

- **If funding has already been awarded or the contract is being processed by the Office of Sponsored Research (OSR) or Industry Contracts Division (ICD), your sponsor is already in the system and the project has an eProposal Proposal or Award number. Check with your department's OSR Staff or ICD Officer to ask how the sponsor is listed in the UC sponsor list and what the Proposal or Award number is. Click here to find your OSR staff and here to find your ICD staff.**
- **If your sponsor is not yet in the list, enter it in the box below.**

☒ Sponsor not in list

**Only** if your sponsor is not yet in the list, type the sponsor's name:

[name] Family Fund; Harvard Research Network on Toxic Stress

**If the funding is administered by the UCSF Office of Sponsored Research, your study will not receive CHR approval until the sponsor and funding details have been added to your application.**

## 7.3 \* This study is currently supported in whole or in part by Federal funding OR has received ANY Federal funding in the past (Help Text updated 9/13):

☐ Yes ☒ No

If **yes**, indicate which portion of your grant you will be attaching:

- ☐ The Research Plan, including the Human Subjects Section of your NIH grant or subcontract
- ☐ For other federal proposals (contracts or grants), the section of the proposal describing human

subjects work

- ☐ The section of your progress report if it provides the most current information about your human subjects work
- ☐ The grant is not attached. The study is funded by an award that does not describe specific plans for human subjects, such as career development awards (K awards), cooperative agreements, program projects, and training grants (T32 awards) OR UCSF (or the affiliate institution) is not the prime recipient of the award

## 8.0 Sites

### 8.1 Institutions (check all that apply):

- ☐ UCSF
- ☐ China Basin
- ☐ Helen Diller Family Comprehensive Cancer Center
- ☐ Mission Bay
- ☐ Mount Zion
- ☒ San Francisco General Hospital (SFGH)
- ☐ SF VA Medical Center (SF VAMC)
- ☐ Blood Centers of the Pacific (BCP)
- ☐ Blood Systems Research Institute (BSRI)
- ☐ Fresno (Community Medical Center)
- ☐ Gallo
- ☐ Gladstone
- ☐ Institute on Aging (IOA)
- ☐ Jewish Home
- ☐ SF Dept of Public Health (DPH)

### 8.2 Check all the other types of sites not affiliated with UCSF with which you are cooperating or collaborating on this project (Help Text updated 9/13):

- ☒ Other UC Campus
- ☒ Other institution
- ☐ Other community-based site
- ☐ Foreign Country

List the foreign country/ies:

### 8.3 Check any research programs this study is associated with:

- ☐ Cancer Center
- ☐ Center for AIDS Prevention Sciences (CAPS)
- ☐ Global Health Sciences
- ☐ Immune Tolerance Network (ITN)
- ☐ Neurosciences Clinical Research Unit (NCRU)
- ☐ Osher Center
- ☐ Positive Health Program

## 9.0 Studies Involving Other Sites

### 9.1 UCSF is the coordinating center:

☒ Yes ☐ No

If **Yes**, describe the plan for communicating safety updates, interim results, and other information that may impact risks to the subject or others among sites:

All study activities will take place at ZSFG hospital. No participants will be consented, enrolled or participate in study activities at UC Berkeley. [name], a member of our study team is based at UC Berkeley. [name] will receive supervision and mentorship from her UC Berkeley advisors throughout the study, but those advisors will not have any contact with research subjects through recruitment, consenting, interviewing, or reviewing identifiable data.

Analysis and Interpretation of Biological Data. Biological specimens collected as part of this research will be analyzed and stored at [name] lab at the Research Center of the Douglas Mental Health University Institute, McGill University in Montreal, Canada. De-identified patient-level survey data collected during the course of the study will be transferred securely to [name] lab at the Research Center of the Douglas Mental Health University Institute, McGill University for use in the interpretation of the biological data analyses. Transfer of patient-level survey data and biological samples are clearly stated in a data sharing agreement with the Research Center of the Douglas Mental Health University Institute, McGill University.

If **Yes**, describe the plan for sharing modification(s) to the protocol or consent document(s) among sites:

See above.

## 9.2 Check any other UC campuses with which you are collaborating on this research study:

- ☒ UC Berkeley
- ☐ UC Davis
- ☐ Lawrence Berkeley National Laboratory (LBNL)
- ☐ UC Irvine
- ☐ UC Los Angeles
- ☐ UC Merced
- ☐ UC Riverside
- ☐ UC San Diego
- ☐ UC Santa Barbara
- ☐ UC Santa Cruz

## 9.3 Are the above UC campuses requesting to rely on UCSF's IRB (check all that apply):

- ☒ Yes (Submit a reliance request through the UC IRB Reliance Registry)
- ☐ No (Complete IRB Approval Certification section)

# 10.0 Outside Site Information

## 10.1 Outside Site Information

Click "Add a new row" to enter information for a site. Click it again to add a second site again to add a third site, a fourth site, etc.

**For Federally-funded studies only, corresponding FWA#:**

**\* The research at this site will be reviewed by:**

- ☒ The non-affiliated site's IRB or a private IRB
- ☐ The non-affiliated site is requesting UCSF to be the IRB of record for this study
- ☐ The non-affiliated site is not engaged in the human subjects research and has provided a letter of support

If the other site's IRB approval letter is available now, attach it to the application. If the IRB approval letter is not yet available, submit it once you receive it.

Or, if the other site is **not engaged** in human subjects research, attach the letter of support to your application.

## 11.0 Study Design

### 11.1 \* Study design (Help Text updated 9/13):

We are proposing an 18-month RCT that collects survey and non-invasive biological data from caregivers accompanying children who are visiting a pediatric urgent care center. Our previous, similar RCT study data collection ended on 8/31/15 as scheduled. Though the social needs-focused intervention is now a routine, standardized part of the pediatric primary care setting, we are proposing a new urgent care-focused randomized controlled trial where we will enroll eligible patients solely from urgent care. In one arm, we will offer the intervention; in the other, we will offer written information on available community resources, which is already above the standard of care. All patients in both arms will be followed over a six month period to capture information about changes in their social needs and health outcomes. Participants will be randomized into intervention or control arms of the study using a stratified randomization method in the computer-based program REDCap.

Activities: Following consent at time of enrollment, at both baseline and 6 mo follow up, we will administer a survey and collect hair, saliva and buccal mucosal cell swabs (from child and adult caregiver).

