## 12.0 Scientific Considerations

### 12.1 Hypothesis (Help Text updated 9/13):

This study has a hypothesis:

☒ Yes ☐ No

If yes, state the hypothesis or hypotheses:

We hypothesize that participants in the SFGH Health Advocacy program will experience improved physical and emotional health (child); improved caregiver mental health; decreases in hair cortisol (child and caregiver); fewer missed school (child) or work days (caregiver); and decreases in acute care utilization (child). Additional outcomes of interest include other stress biomarkers, like salivary inflammatory cytokines and DNA genotyping and methylation.

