### 12.3 Statistical analysis:

**Descriptive Analyses & Missing Data.** Descriptive analyses will include family demographics, biomarker, child and caregiver health, and family social needs. Data will be inspected for outliers and out-of-range values. Examination of distributions may prompt transformations, where they are defensible and are a component of the best available analysis strategy. Although protocols have been designed to promote retention, some attrition is inevitable. We will perform analyses to determine whether differential attrition occurred by patient characteristics. Likelihood based approaches (e.g. GLMMs) will be used to handle missing data. This approach fits models to all available data and invoke the relative assumption that the data are missing at random.

Background demographics will be examined to describe the sample and will be included in multivariate analysis if they are related to the outcome at  $p < .2$  or associated with dropout. Correlations among variables will be examined and redundant measures will be combined or eliminated to avoid multicollinearity. We will compare participants randomized to the two groups on caregiver and child characteristics using t-tests and chi-square tests.

**Assessment of Outcomes:** We will fit regression models for cross-sectional and longitudinal outcomes. Changes from baseline to follow-up on the primary outcomes will be estimated with linear mixed models and generalized linear models with generalized estimating equations (e.g., SAS PROC MIXED, GENMOD, SAS Institute Inc., 1999). Generally, we seek to model longitudinally the trajectory of the primary outcomes as a function of time. We begin by fitting *base* models, those with intervention group and minimum covariates and, for longitudinal models, the most restricted residual covariance structures. We will then consider additional baseline demographic or family predictors, and baseline family predictors-by-time interaction in subsequent models to examine moderators of change. Similar models will be used to examine each of the primary outcomes outlined. Empirical contributions to model selection decisions will include reference to information criteria (e.g., Akaike's). We will examine change from baseline for each outcome as the dependent variable.

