If a family is randomized into the intervention group, the HARA will have access to the social needs screening results obtained through the health survey. The HARA will proceed with the health advocacy intervention following the procedures of the SFGH Health Advocacy program and attempt to address unmet needs identified by the caregiver in the survey. This involves working directly with these participants to identify and address any social needs the family may have such as access to food, living conditions and financial security. This may also include providing referrals to outside agencies, referral to legal aid within the clinic, help with applications for social benefits, or other services (See attached HARA Initial Action Plan and FollowUp Survey). Participants in the intervention group who are also ZSFG Pediatric Primary Care patients will have receipt of any direct assistance provided by the HARA documented in their child's medical record indicating services provided. All members of the intervention group will receive a written handout containing information about community resources related to the social needs we ask about in the survey.

The HARA will follow-up with members of the intervention group for a maximum of 3 months by telephone to continue to assess progress towards addressing social needs and to provide further help as needed. When relevant, HARA will send blank program forms to families or other publicly available program information via email or U.S. post to members of the intervention group. If a patient does not respond to telephone follow-ups for over 1 month, HARA may also send secure email to initiate follow-up contact.

If participant dyads are randomized into the control group, the HARA will provide the family with a written handout containing information about community resources related to the social needs we ask about in the survey.

Complete scripts for the biomarker specimen collections are found in Appendices A and B. Following surveys, hair, saliva and buccal mucosal cells will be collected non-invasively. These measures will be obtained immediately after enrollment and at the six month follow up timepoint.

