**19.4 Benefits to society:**

If our hypotheses are correct, then connecting patients with health advocate navigators will decrease social needs, decrease caregivers' missed work days, and improve child school attendance, decrease hair cortisol and salivary/buccal mucosal cell inflammatory markers, and decrease avoidable health care utilization.

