### 21.2 Additional vulnerable populations:

- ☒ Children
- ☐ Subjects unable to consent for themselves
- ☐ Subjects unable to consent for themselves (emergency setting)
- ☐ Subjects with diminished capacity to consent
- ☒ Subjects unable to read, speak or understand English
- ☐ Pregnant women
- ☐ Fetuses
- ☐ Neonates
- ☐ Prisoners
- ☒ Economically or educationally disadvantaged persons
- ☐ Investigators' staff
- ☐ Students

Explain why it is appropriate to include the types of subjects checked above in this particular study:

We are conducting this study with caregivers of patients in the ZSFG Peds Urgent Care Clinic, where many caregivers are unable to read/write English, and many are socioeconomically disadvantaged. Since the aim of the study is to document the impact of better connect patients who need resources with available community services, it is essential to recruit these families. The study is aimed at improving pediatric health outcomes so recruiting from pediatric populations is an additional requirement. We have checked the "children" box because we are accessing medical records of the index child (child receiving care at ZSFG on day of enrollment) at 12 months following enrollment.

Describe the additional safeguards that have been included in the study to protect the rights and welfare of these subjects and minimize coercion or undue influence:

We are consenting caregivers who are parents or legal guardians who have knowledge of the pediatric patients' living environment. This should minimize risks to the rights and welfare of pediatric patients. We are adding an adolescent assent requirement for using EMR utilization data at 12 months following household enrollment in the study. EMR data will be linked with study survey and biomarker data. We will obtain HIPAA authorization from all participants for whom these links will be made.

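### Child salivary cytokines: the baseline sample is taken at an urgent care visit, so the change-from-baseline rule in 12.3 adds illness variance to an otherwise unbiased comparison

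*Protocol*

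**What the plan says.** Section 11.1 describes a trial that "collects survey and non-invasive biological data from caregivers accompanying children who are visiting a pediatric urgent care center". On the source of participants, the same section states that "we will enroll eligible patients solely from urgent care". On sampling, it states that "at both baseline and 6 mo follow up, we will administer a survey and collect hair, saliva and buccal mucosal cell swabs"; both members of the dyad give these samples. Section 21.2 defines the enrolled child as the "index child (child receiving care at ZSFG on day of enrollment"). On timing, 16.1 says: "These measures will be obtained immediately after enrollment and at the six month follow up timepoint". The follow-up is an arranged research visit, allowed from 5 to 9 months, in a research room, a community location or (16.7) the home.

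The exclusions in 14.7 that concern the reason for the visit cover only child protective clearance and child abuse examinations. The saliva procedure in Appendix B of 16.1 checks for food and gum, not for illness or medication.

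Section 12.1 places cytokines in a second tier: "Additional outcomes of interest include other stress biomarkers, like salivary inflammatory cytokines and DNA genotyping and methylation". Section 12.2 lists child and caregiver stress and immunologic biomarkers as its second aim. Section 19.4 expects, if the hypotheses are right, that the programme will "decrease hair cortisol and salivary/buccal mucosal cell inflammatory markers, and decrease avoidable health care utilization". Section 12.3 closes with the rule: "We will examine change from baseline for each outcome as the dependent variable".

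**The concern.** Cytokines are meant here as a marker of social stress. A child seen in urgent care may have an infection or injury that raises them for reasons unrelated to stress. By the scheduled visit about six months later, that illness will usually have passed. The two samples are then taken in different states, and their difference contains recovery as well as any effect of the programme.

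Two things are at stake. The first is precision: subtracting a baseline that carries extra illness variance puts that variance into the contrast, and a real effect becomes harder to see. The second is interpretation: cytokines could fall in both arms with no programme effect, and 19.4 predicts a fall. The point concerns the child's saliva. The caregiver is not the patient, and hair cortisol, which integrates earlier months, is much less affected.

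**Working it through.** **1. The plan's own figure.** Section 14.4 gives 362 per arm, 30% attrition, two-sided alpha 0.05 and d = 0.25. Then 362 × 0.70 = 253.4, so 253 per arm. Power = Φ(0.25 × √(253/2) − 1.96) = Φ(0.85) = 0.803 (0.801 with the t distribution). The stated 80% reproduces. It concerns social needs and cortisol; the protocol gives no power for cytokines, so the present point leaves that figure intact.

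**2. Variance of each analysis.** The documents give no cytokine SD, correlation or share of ill children, so the inputs below are assumptions. On the scale analysed, let the usual-state SD be 1 at both visits and the usual-state correlation be r. Let illness add an independent component with SD k to the baseline only, in both arms alike.

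- Change score: 1 + (1 + k²) − 2r = 2 + k² − 2r
- Change score with no illness: 2 − 2r
- Six-month value alone: 1
- Six-month value adjusted for baseline: 1 − r²/(1 + k²)

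| r | k | Change, no illness | Change, with illness | Six-month alone | Baseline-adjusted |
|---|---|---|---|---|---|
| 0.2 | 0.5 | 1.60 | 1.85 | 1.00 | 0.97 |
| 0.4 | 1.0 | 1.20 | 2.20 | 1.00 | 0.92 |
| 0.5 | 1.0 | 1.00 | 2.00 | 1.00 | 0.88 |
| 0.4 | 1.5 | 1.20 | 3.45 | 1.00 | 0.95 |

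Relative to the six-month value alone, the standard error of the change contrast is √1.85 = 1.36, √2.20 = 1.48, √2.00 = 1.41 and √3.45 = 1.86.

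Part of this is the ordinary cost of a change score. The factor due to illness is 1.85/1.60 = 1.16, 2.20/1.20 = 1.83, 2.00/1.00 = 2.00 and 3.45/1.20 = 2.88.

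**3. The same in power terms.** Assume r = 0.5, 253 per arm and a raw effect of 0.25 usual SDs.

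| Illness variance k² | Change-score SD | Power, change | Power, baseline-adjusted |
|---|---|---|---|
| 0 | 1.00 | 0.80 | 0.90 |
| 0.5 | 1.22 | 0.63 | 0.87 |
| 1 | 1.41 | 0.51 | 0.85 |
| 2 | 1.73 | 0.37 | 0.84 |

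**4. Is the contrast biased?** A simulation of 4,000 trials with no programme effect assumed 60% of children ill at baseline in both arms, with values raised by 1.5 SD on average, and r = 0.5. The mean within-arm change was −0.90 (as expected from 0.6 × 1.5 = 0.90). The mean difference between arms was 0.00 and the type I error 0.049. Recovery shows within arms and cancels between them.

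**The case against.** The strongest reply is that the randomized comparison is sound. Baseline samples are taken before allocation (16.1), and 14.4 bases the test on the difference between groups in change. That stands. A reader might infer that the effect estimate is biased, or that 19.4 announces a within-arm test; the documents support neither. Section 19.4 states a causal expectation about the programme, and no within-arm cytokine test is planned.

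The outcome is also peripheral. Cytokines are additional outcomes in 12.1, the power statement does not rest on them, and 17.2 ties the analyses of the stored samples to available funding. One can also read the closing sentence of 12.3 as confined to the primary outcomes discussed just before it, although its wording covers each outcome. This limits the weight of the point. It does not remove it, because immunologic biomarkers are a numbered aim.

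A reader might also infer that no record of the illness exists. That goes too far. Sections 20.3 and 21.2 link the child's medical record with survey and biomarker data, and the survey covers physical health (16.2), though its items are not shown. What is absent is a stated plan to use such information.

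Nor can one say that baseline cytokines simply measure the presenting illness. Not every urgent care visit is for an inflammatory condition, and no share is given. Section 14.6 also admits primary care patients, which must be reconciled with 11.1.

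Finally, ordinary baseline adjustment already removes the change-score penalty: at r = 0.4, k = 1 the variance drops from 2.20 to 0.92. This is correct, and it is why the fix keeps the baseline as a covariate instead of discarding it.

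**Conclusion.** The point holds as a loss of precision in one additional outcome. Baseline child cytokines can reflect the illness that brought the child in, and an unadjusted change score passes that variance into the comparison between arms. At r = 0.4 and k = 1 the variance is 2.2 for change, against 1.2 for change without illness, 1.0 for the six-month value and 0.92 for the baseline-adjusted six-month value. Over the assumed range, illness multiplies the change-score variance by about 1.2 to 2.9.

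These sizes rest on assumed r and k, on illness affecting only the baseline, and on its being independent of the child's usual level. The direction does not depend on the exact values: in this model any k above zero makes the change score less precise, and the baseline-adjusted value is never worse than the six-month value alone. No bias between arms and no effect on the stated power for social needs or cortisol is claimed. The change is worthwhile because it costs almost nothing.

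**What to change.** In 12.3, for child salivary cytokines, replace change from baseline with a comparison between arms of the six-month value. Adjust it for the baseline value and for baseline acute-illness status, taken from the visit reason in the linked chart. An interaction between baseline value and illness status is optional; it lets the baseline count for more in children who were well. Add that a fall within an arm will not be interpreted as an effect of the programme.

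Illness at the six-month collection may be recorded for description or for a clearly labelled sensitivity analysis. It should not be adjusted for, or used to exclude children, in the main analysis. It arises after randomization and the programme may affect it: 12.1 hypothesizes better child physical health and less acute care use. Conditioning on it could remove part of the effect or introduce selection.

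The cost is a few sentences in 12.3, a rule for classifying visit reason, and that field in the planned record extract. If illness at six months is to be described, one survey item is added unless the survey already has one. Sample size, eligibility and sampling do not change.
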